### Surgical quality control

Each center must be a tertiary hospital that has performed at least 20 minimally invasive RTAs and 20 THs in each of the past three years. Surgeons who are skilled in both procedures and have performed each procedure at least 20 times will be eligible for the trial. To ensure surgical quality and facilitate whole-course monitoring, photographs should be taken during each operation to show the integrity of lymph node dissection and tumor resection. If the R0 resection rate is found to be low or the effect of dissected lymph nodes cannot meet requirements during the monitoring process, it will be necessary to analyze the problems and determine the possible reasons.

### Pathological quality control

For the pathological examination to be of high quality, all samples from lymph node stations and peritumoral stations will be examined and analyzed by the pathology department. The surgeon will pack every lymph node station during the lymph node dissection, allowing the pathologist to examine the station individually. In contrast, the peritumoral stations will be marked as a whole rather than individually resected to ensure that the margin of resection can be accurately analyzed. Each center’s lead pathologist will review the slides of ten percent of all cases. Except for the tissue for pathological analysis, which needs to be stored in wax blocks for 30 years, the rest of the tissue samples submitted for examination will be destroyed prior to pathological analysis, while all blood samples will be destroyed after pathological analysis.

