## Methods

### Objective

The purpose of this trial is to compare RTA with TH for resectable Siewert II AEGs based on surgical safety, clinical efficacy and prognosis. The primary outcome of the study will be the 3-year disease-free survival (DFS) to assess the oncological safety of the procedure. The secondary outcomes will be 5-year overall survival (OS), incidence of postoperative complications, postoperative mortality, local recurrence rate, number and location of removed lymph nodes, surgical Apgar score, duration of the operation and the quality of life (QOL) score.

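### Tissue not embedded at first sampling is to be destroyed before pathological analysis, so a missed node or poorly sampled margin could not be re-sampled (minor)

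*Protocol article*

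**What the plan says.** Everything on specimen handling stands in one paragraph of the protocol article, Pathological quality control. It opens with a commitment that "all samples from lymph node stations and peritumoral stations will be examined and analyzed by the pathology department". Node stations are packed separately by the surgeon so that each can be examined on its own. The tissue around the tumor is treated differently: "the peritumoral stations will be marked as a whole rather than individually resected to ensure that the margin of resection can be accurately analyzed".

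The paragraph then sets one re-check, "Each center’s lead pathologist will review the slides of ten percent of all cases", and closes with a sentence on retention that has three parts:

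- What is kept: "Except for the tissue for pathological analysis, which needs to be stored in wax blocks for 30 years".
- What happens to other submitted tissue: "the rest of the tissue samples submitted for examination will be destroyed prior to pathological analysis".
- What happens to blood: "all blood samples will be destroyed after pathological analysis".

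Two other places depend on the specimen. The Objective section lists "number and location of removed lymph nodes" among the secondary outcomes. The Intervention section treats the resection margin as central to judging whether the operation was curative.

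**The concern.** The order of events is the problem. A second look at a specimen is usually prompted by the first result, for example a node yield that seems too low or a margin that cannot be judged from the slides. If the unembedded remainder is discarded before analysis, that result arrives when there is nothing left to go back to. The wording also sits badly with the opening commitment, because tissue submitted for examination cannot all be analyzed if part of it is destroyed first.

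At stake is whether two measurements can be completed when the first attempt falls short: the lymph node count, which bears on the trial's hypothesis that RTA gives better mediastinal dissection, and the margin assessment.

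**Working it through.** No figure in the protocol depends on this sentence, so there is nothing to recompute. The check is to set the statements side by side and follow a specimen through them.

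**Step 1: compare the statements.**

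| Material | Stated handling | Timing relative to analysis |
|---|---|---|
| Node-station and peritumoral samples | All examined and analyzed | Not applicable |
| Tissue taken for analysis | Wax blocks, 30 years | Kept after it |
| Other tissue submitted | Destroyed | Before it |
| Blood | Destroyed | After it |

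The third row conflicts with the first unless the remainder contains nothing from the node or peritumoral stations, which the text does not say. The third and fourth rows come from the same sentence and give opposite timings. No other section corrects either.

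**Step 2: what survives at the moment the slides are read.** Under the literal rule, only the blocks and the slides cut from them. The blocks hold what was chosen at first sampling and nothing else.

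**Step 3: what can still be done if the first result is inadequate.**

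- The tissue was embedded but misread or badly cut: recoverable. The block can be re-cut and re-read for 30 years.
- A node lay in submitted tissue that was not embedded: not recoverable.
- The relevant part of a margin was not embedded: not recoverable.
- A station was never dissected or never packed: not recoverable under any retention rule, so this case does not count against the sentence.

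**Step 4: where the exposure lies.** Node stations arrive separately packed and are to be examined one by one. If that is done, little of their tissue should end up in the remainder. The part marked as a whole is larger and is handled in one piece, so incomplete first sampling is most plausible there.

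**Step 5: does another provision close the gap?** The lead pathologist's check covers slides in 10% of cases. It can correct a misreading, and it can show that sampling was thin, but it cannot obtain tissue that was never embedded. In Table 1 pathology appears once, at discharge, and no later specimen examination is scheduled.

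**Step 6: which results are touched.** The lymph node secondary outcome and the margin assessment draw on the specimen directly. The primary outcome, 3-year disease-free survival, is followed through clinic visits, imaging and endoscopy, so residual tissue does not enter it directly.

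**The case against.** The strongest reply is that this is a slip of drafting or translation. The sentence is loosely written: it ties the disposal of blood to pathological analysis, although blood plays no part in the specimen examination that the paragraph describes. Taken literally it clashes with the paragraph's own opening, and a competent pathology department may well not act on it. That is plausible, and it is a reason to rate the point low. It does not remove the point, because the opposite timings for tissue and blood within one sentence read as intended and nothing else in the article corrects them.

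A second reply is that retention procedures belong in a full protocol or pathology manual. That would answer a complaint that the rule is absent. Here a rule is stated, and it is the stated rule that gives the worse result.

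A reader might also infer more than the text supports:

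- **That node counts, margins and stage can no longer be re-derived at all.** The 30-year blocks rule this out. Only tissue never embedded is lost.
- **That the surgical monitoring is disabled.** The Surgical quality control section says "If the R0 resection rate is found to be low or the effect of dissected lymph nodes cannot meet requirements", the causes must be analyzed. That concerns surgical performance across cases and was never a means of re-sampling one patient's specimen.
- **That a definite number of the 212 patients would be affected.** Any such number would be an assumed re-sampling rate multiplied by enrollment, and the documents contain no such rate. Enrollment also overstates the number of specimens, since the termination criteria foresee patients found inoperable after registration.
- **That the error would differ between the arms.** The two approaches may yield different specimens, but nothing in the documents shows unequal sampling, and the pathologists are to be blinded to allocation.

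**Conclusion.** The point holds in a limited form and is minor. As written, the paragraph promises full examination and also orders the remaining submitted tissue to be destroyed before analysis. A site that followed it literally could re-read what it had embedded, but could not sample again for a missed node or an inadequately sampled margin.

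The conclusion rests on two assumptions: that sites act on the wording as it stands, and that some submitted tissue is not embedded at first sampling. If every submitted sample were fully embedded, there would be no remainder and no loss.

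Its size cannot be given as a patient count. It bears on one secondary outcome and on the margin assessment. R0 status and nodal stage are not themselves listed outcomes, and the primary comparison is not directly affected.

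**What to change.** Reconcile the two statements, and change the retention sentence so that unembedded tissue is destroyed only once the pathology report has been signed off. In the 10% of cases chosen for slide review, it should be kept until the lead pathologist's review is complete. This gives tissue the same order of events that the sentence already sets for blood. If the present wording is a slip, the same edit corrects it.

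The cost is one amended sentence, carried into any pathology manual, and short storage of fixed tissue at each center. The 30-year block retention, the slide review and the sample size stay as they are.

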### Postoperative treatment

There will be no difference in postoperative treatment between the two groups. Analgesia and antibiotics will be administered according to the standards of each trial site. The surgeons at each participating institution will be responsible for implementing postoperative fluid rehydration and nutritional support. Patients with advanced AEG will routinely receive postoperative adjuvant chemotherapy. Each trial center will discharge patients in accordance with their standard practices.

### Outcome measures

The primary outcome is a comparison of 3-year disease-free survival (DFS) between the two groups. The secondary outcomes of the trial included 5-year overall survival (OS), incidence of postoperative complications, postoperative mortality, local recurrence rate, the number of lymph nodes, quality of life (QOL) score, surgical Apgar score and duration of the operation. All types of postoperative complications will be defined by the Esophageal Complications Consensus Group (ECCG) (22) and classified by the Clavien−Dindo grading system (23). A variety of questionnaires will be used to assess QOL. General health aspects will be measured by the SF-36 and CAT EORTC QLQC30, whereas esophageal health will be assessed by the CAT EORTC QLQ-OES18 (24).

### Data collection and management

The clinical data will be completely, timely, accurately and truthfully recorded in the CRF table by the study coordinator. Any changes that are made will be signed and dated by the person concerned, but these changes will never involve the original data. Since randomization is centralized, each participating center will use thestratified-field block-randomization method (25). The study coordinator randomly assigned study populations meeting inclusion and exclusion criteria to either the RTA group or the TH group based on random numbers drawn from the hidden envelope. And each center will assign another study coordinator to be responsible for the data entry and uploading. The project sponsor or the clinical coordinator on behalf of the sponsor will be in regular contact with the center to provide information and technical support. In this way, the investigators can be supervised to strictly implement the study protocol, and to a certain extent, the accuracy of the clinical information on the CRFs can be verified. Authorized representatives of the project undertaking units, regulatory authorities, and ethics committees have the right to audit and inspect the works of each research center at any time, including original data verification. The purpose of an audit or inspection by the project undertaking unit is a comprehensive and targeted review of all study-related activities and documentation, which can guarantee that these activities are supervised in accordance with the guidelines of the research proposal and other regulatory requirements, and the clinical data are accurately analyzed, recorded and reported.

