### The inclusion criteria for this study are as follows

·Siewert II AEG confirmed histologically·Both RTA and TH can safely resect the tumor·Pretreatment stage cT_1-4a_, N_0-3_, M_0_ (referring to the 8th AJCC TNM staging system)·Aged 18-75·The Eastern Cooperative Oncology Group (ECOG) performance status ranges from 0 to 2·American Society of Anesthesiologists (ASA) <4·Laboratory tests: hemoglobin > 90 g/L, white blood cells > 3×10^9^/L, platelet > 100×10^9^/L, glomerular filtration rate > 60 ml/min, total bilirubin < 1.5x upper level of normal (ULN), aspartate aminotransferase (AST) and alanine aminotransferase (ALT) < 2.5x ULN·Informed consent is voluntarily signed by the patients and their families

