### Intervention

An equal number of patients will be randomly assigned to the RTA and TH groups. Details of the surgery are determined by the surgeons at each center as long as the tumor can be resected completely. If the tumor is difficult to be resect under minimally invasive conditions, the surgical strategy will be adjusted at that time.

The TH approach will be performed by distal esophagectomy and mediastinal lymph node dissection *via* the diaphragmatic hiatus under laparoscopy, whereas the RTA approach will be performed under thoracoscopy. The resection margin is a key indicator for evaluating the curative effect of surgery. The 5-year mortality of patients with positive resection margins is significantly higher than that of patients with negative resection margins (21).

According to the NCCN guidelines (6) and the Chinese expert consensus, for Siewert type II AEG with cT1 stage, the upper esophageal resection margin is recommended to be at least 2 cm away from the tumor, while for patients with cT2 stage or above, the upper esophageal resection margin is recommended to be at least 5 cm away from the tumor if the RTA approach is performed and at least 3 cm if the TH approach is performed. For patients in the former staging category, the lower resection margin is recommended to be at least 3 cm, while for patients in the latter staging category, a minimum of 5 cm is required to meet the surgical requirements. Laparoscopic proximal gastrectomy can be performed regardless of the surgical approach if the above criteria for the lower resection margin are met and at least more than half of the residual stomach remains.

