### Sample size calculation

To calculate the required sample size, the primary outcome is taken into account. According to a previous retrospective study (26), the 3-year disease-free survival (DFS) is 47.6% for RTA and 32% for TH. Then, we calculated 212 patients (106 in the RTA group and 106 in the TH group) need to be enrolled in this trial using a one-sided two-sample t-test. The conventional type I error is 5%, the statistical power is 90%, and the dropout rate is 15%. Prior to participating in the trial, every center should report the number of patients likely to be recruited with reference to the number of patients admitted in recent years for Siewert II AEG.

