### Statistical analysis

Standard descriptive statistics will be used to analyze the qualitative and quantitative variables, including the relative and absolute frequencies, means, medians, standard deviations, and interquartile ranges. Continuous variables will be compared using Student’s t-tests or Mann−Whitney U tests, while categorical variables will be compared using chi-square tests or Fisher’s exact tests. A confidence of 95% will be considered suitable for analysis. Statistical significance will be defined as a p value of 0.05 or less. IBM SPSS (Version 28, Chicago, USA) will be used to conduct the statistical analysis.

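### Randomisation is stratified, but none of the comparisons the article names uses the strata; this makes them somewhat conservative and costs a little power

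*Protocol article*

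**What the plan says.** **Allocation.** Under Data collection and management, "each participating center will use thestratified-field block-randomization method". No stratification factor or block size is given. Six centres are listed under Study design, so centre is the only stratum that can be inferred.

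**Analysis.** The Statistical analysis section sorts tests by type of variable. "Continuous variables will be compared using" Student's t or the Mann-Whitney U test, and "categorical variables will be compared using chi-square tests" or Fisher's exact test. It names no stratified, covariate-adjusted or time-to-event method. Significance is set at p of 0.05 or less, with no sidedness stated.

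**Primary outcome.** Under Outcome measures, "The primary outcome is a comparison of 3-year disease-free survival (DFS) between the two groups". The Sample size calculation assumes that "the 3-year disease-free survival (DFS) is 47.6% for RTA and 32% for TH" and sizes the trial "using a one-sided two-sample t-test" at 5% type I error, 90% power and 15% dropout, giving 212 patients.

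**Sources of variation.** Under Intervention, "Details of the surgery are determined by the surgeons at each center as long as the tumor can be resected completely". Analgesia, antibiotics and discharge also follow local practice (Postoperative treatment). Eligibility runs from cT1 to cT4a and N0 to N3, "referring to the 8th AJCC TNM staging system". Stage is a pretreatment criterion, and tumour classification is a preoperative item in Table 1.

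**The concern.** Stratified blocks force the arms to be nearly balanced within each stratum. Differences in prognosis between strata then cancel from the treatment comparison, so its true sampling variance is smaller. A test that ignores the strata still counts that between-stratum variation as noise. Its standard error is too large to the extent that the strata are prognostic, and the precision bought by the design is not used.

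The article gives some reason to expect variation by centre (technique and perioperative care are partly local) and by stage (the eligible range is wide, recommended margins depend on cT, and advanced disease routinely receives adjuvant chemotherapy). It quantifies neither. At stake are a few points of power in a trial with none to spare, and a choice between adjusted and unadjusted results that is better fixed before outcomes are seen, because surgeons, patients and coordinating researchers are unblinded.

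**Working it through.** **1. The plan's own figure.** Inputs from the Sample size calculation: p1 = 0.476, p2 = 0.32, difference 0.156, mean 0.398, one-sided 5%, 90% power, 15% dropout.

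n per arm = [1.645·√(2·0.398·0.602) + 1.282·√(0.476·0.524 + 0.32·0.68)]² / 0.156² = (1.139 + 0.876)² / 0.02434 ≈ 167. Dividing by 0.85 gives 197 per arm, 394 in total. The stated 212 in total is not reproduced by this or by the other variants tried (means formula 390–398, Schoenfeld/Freedman 366–378, continuity-corrected proportions 424).

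With 212 × 0.85 ≈ 180 evaluable patients, 90 per arm, one-sided power = Φ[(0.156·√90 − 1.139)/0.683] = Φ(0.50) ≈ 69%. Two-sided at 0.05 it is 57%. This is a separate problem; here it only sets the baseline for the comparison below.

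**2. Why the unstratified test is conservative.** Let V be the variance of the stratum DFS rates. With balance inside strata, the true variance of the difference is proportional to p(1−p) − V, while the chi-square test uses p(1−p). Under the null the z statistic therefore has variance 1 − r, with r = V / [p(1−p)], and

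actual one-sided error = 1 − Φ(1.645/√(1 − r)).

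Here p(1−p) = 0.398·0.602 = 0.2396. The documents give no centre effect. I assume six equal centres evenly spaced on the logit scale (at ±0.292, ±0.876 and ±1.46 SD), with mean rate 0.398:

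| Assumed centre SD (logit) | Range of centre DFS rates | V | r | Error, formula | Error, simulation |
|---|---|---|---|---|---|
| 0.3 | 29.7% to 50.4% | 0.0050 | 0.021 | 4.8% | 4.8% |
| 0.5 | 23.7% to 57.2% | 0.0133 | 0.056 | 4.5% | 4.7% |
| 0.8 | 16.2% to 66.6% | 0.0309 | 0.129 | 3.9% | 4.0% |

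Formula and simulation agree within Monte Carlo error (about 0.2 points).

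**3. Power, 3-year DFS as a binary outcome.** Simulated 1:1 randomisation in blocks of 4 (assumed), 180 evaluable patients, 47.6% v 32%, one-sided 5%. The unstratified test is compared with a Mantel-Haenszel test stratified by the randomisation strata (8,000 runs per row for centre only, 4,000 with the extra factor; Monte Carlo SE about 0.5–0.7 points).

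| Strata and assumed effects | Unstratified | Stratified | Gain |
|---|---|---|---|
| Centre, SD 0 | 69.6% | 69.0% | −0.6 |
| Centre, SD 0.3 | 68.8% | 69.0% | +0.2 |
| Centre, SD 0.5 | 69.4% | 70.6% | +1.2 |
| Centre, SD 0.8 | 70.8% | 74.0% | +3.2 |
| Centre 0.3 + binary factor, log-OR 0.7 | 70.9% | 71.6% | +0.7 |
| Centre 0.5 + log-OR 1.0 | 69.4% | 72.2% | +2.8 |
| Centre 0.5 + log-OR 1.5 | 70.0% | 74.3% | +4.3 |
| Centre 0.5 + log-OR 2.0 | 70.4% | 77.2% | +6.8 |

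Across the last four rows the unstratified test's type I error was 5.0%, 4.1%, 3.4% and 2.9%. The stratified test stayed at about 4.5% to 5.2% throughout. With two-sided testing and centre strata only, the gains run from −0.5 (57.8% to 57.3%, SD 0) to +4.7 points (58.0% to 62.7%, SD 0.8).

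**4. Cross-check with a time-to-event outcome.** HR = ln 0.476 / ln 0.32 = 0.651, N = 212, 15% dropout, one-sided log-rank, 4,000 runs per scenario, centre SD 0.3 on the log-hazard:

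- Stage gap 1.0 on the log-hazard: 67.6% unstratified, 68.5% stratified by centre, 73.4% by centre and stage.
- Stage gap 0.5: 70.6% unstratified, 72.0% by centre and stage.
- No stage effect: 73.2% unstratified, 71.2% by centre and stage, a loss of 2 points.

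Of the 5.8 points in the first case (73.4 − 67.6), 0.9 comes from centre (68.5 − 67.6) and 4.9 from the assumed stage effect.

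**The case against.** The strongest reply is that one generic paragraph in a condensed article is not the analysis plan. It does not say which test applies to the primary comparison, it does not rule out adjustment, and a full protocol or SAP may supply both. That stands against any claim that every analysis in the trial is unstratified, and silence on covariates alone would be no finding. It does not remove the mismatch: the article states a stratified allocation and names its tests, and those tests do not use the strata.

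Second, no stratification factor is named, and nothing makes cT or cN a stratum or gives its effect on DFS. This stands. A reader might infer that strong, established prognostic factors are being ignored at a cost of about 5 points of power. The documents do not support that: the figure depends on an assumed log-hazard gap of 1.0, and centre alone accounts for about 1 point of it.

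Third, a reader might infer that wrong standard errors threaten the validity of a positive result. They do not; the error is in the conservative direction. Nor is an attenuated hazard ratio a fault of this plan. The Statistical analysis section names no hazard ratio, and an unadjusted difference in 3-year DFS is a valid marginal estimate.

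Fourth, the gain is not free. Six centres by two stage groups make 12 strata for 212 patients, and power falls slightly if the factors do not matter. This also stands and belongs with the fix.

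**Conclusion.** The point holds as a modest mismatch between design and analysis. I am confident that the named tests ignore the stated stratification and that the consequence is conservative. I am less sure of its size, which rests on assumed centre and stage effects, a block size of 4 and equal expected stratum sizes. If only centre is a stratum and its effect is modest, the loss is about 0 to 1 point of one-sided power, within simulation error. It reaches about 3 points at a centre SD of 0.8, and about 1 to 7 points if a prognostic factor is also a stratum.

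A reader might connect this with the power deficit and expect stratification to cure it. It does not: the highest stratified figure with 180 evaluable patients is 77%, against the stated 90%. That shortfall should be dealt with separately and should not raise the weight of this point.

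**What to change.** In Data collection and management, name the stratification factors actually used. In Statistical analysis, state that:

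- the primary 3-year DFS comparison is stratified by those factors: a stratified log-rank test with a stratified Cox model, or a Mantel-Haenszel comparison if 3-year DFS is analysed as binary;
- adjustment for baseline cT and cN category is pre-specified, using the preoperative assessment and not the pathological stage;
- the unadjusted tests now listed are kept as sensitivity analyses;
- small centres are pooled by a rule fixed before outcome data are seen.

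The cost is wording only; no new data are needed. The statistical downside is a loss of up to about 2 points of power if the factors turn out to have no effect.
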